## Methods

### Study Design

REATTACK is a prospective cohort study with a 3-month follow-up period. The participants are patients who had TIA within 7 days of onset diagnosed by two neurologists. Brain DWI and PWI assessments will be completed within 24 h of admission, and *T*_*max*_ > 4 s > 10 ml is used to determine the presence of hypoperfusion. According to baseline MRI-PWI examination, the patients are divided into the PWI positive and PWI negative groups. DWI, PWI, fluid-attenuated inversion recovery (FLAIR), and magnetic resonance angiography (MRA) examinations will be repeated 7 days later. The main outcomes are the incidence of recurrent TIA within 7 days and in 3 months, and the mRS score in 3 months.

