## Abstract

**Background:** Transient ischemic attack (TIA) has a high incidence of recurrent vascular events. Hypoperfusion is one of the factors that are closely correlated with 7-day recurrence of TIA. This study aimed to evaluate the power of hypoperfusion shown on magnetic resonance (MR) perfusion imaging in predicting the incidence of 7-day recurrence of ischemic events after TIA.

**Methods/Design:** REATTACK is a prospective multi-centered cohort study on the correlation between MR perfusion and TIA recurrence. Ninety patients aged ≥18 years with recent (<7 days after onset) clinical TIA will be continuously included. All the patients will undergo diffusion-weighted imaging (DWI) and perfusion-weighted imaging (PWI) assessments within 24 h after the onset of TIA. The subjects will then be divided into a PWI positive group and a PWI negative group according to the time-to-maximum of the residue function (*T*_*max*_). PWI will be repeated after 7 days and in 3 months. The primary clinical outcome will be the recurrence of TIA within 7 days after the onset of TIA. Secondary outcomes will be the recurrence of TIA in 3 months and modified Rankin scale (mRS) score. A chi-square test will be performed to compare the difference in the incidence of recurrent TIA between the two groups, and rank sum test in the mRS score. Multivariate logistic regression will be simultaneously performed to analyze the risk factors for the recurrence of TIA.

**Discussion:** The results of this study will confirm whether abnormal *T*_*max*_ helps to identify the patients with TIA who have high risks of recurrent ischemic events. This would largely improve the prognosis of patients with TIA.

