### Procedures

Ninety patients will be recruited in the next 1.5 years based on the calculation of the authors. Baseline assessments will be completed when the participants visit the neurology clinic of Shanghai Fourth People's Hospital or Tongji Hospital. The first PWI will be completed within 24 h after onset, and the subsequent PWI will be completed on the 7th day ± 2. Three visits to the hospital are required, which include the first visit for randomization (baseline) and the next two for repeat PWI on day 7 ± 2 and follow-up on 90 ± 7 days. The incidence of recurrent vascular events will be collected from all the patients on the second and third visits. Meanwhile, etiological subtypes (large artery occlusive disease, small vessel disease, cardioembolism, etc.) should also be considered for reasons of early recurrent stroke (Purroy et al., 2007). Baseline and follow-up assessments are summarized in Table 1.

**Table 1 T1:** Trial schedule.

**Assessment**	**Screening (within 24 h of symptoms onset)**	**Visit 1**	**Visit 2**	**Visit 3**
		**Baseline**	**Day 7 ± 2**	**Day 90 ± 7**
Demographic characteristics	×			
ABCD2 score (for TIA)	×			
Modified Rankin Scale	×		×	×
Focused medical history	×^a^			
Current medications	×^b^		×	×
MRI scan	×			
MRI PWI		×	×	×
Laboratory tests	×			
Electrocardiograph (ECG)	×			
Inclusion/Exclusion criteria	×			
Signed informed consent	×			
AEs/SAEs^c^		×	×	×
Incidence of recurrence			×	×

*AE, adverse event; SAE, serious adverse event; TIA, transient ischemic attack; ABCD2, a risk assessment tool designed to improve the prediction of short-term stroke risk after transient ischemic attacks*.

a *Relevant existing data from admission to hospital will be reviewed and recorded into the CRF. Included are concomitant diseases and medical history*.

b *The medications used during the trial should be recorded*.

c *SAEs will be recorded from the time of informed consent. AEs of interest and endpoints will be collected from the time of admission to the hospital*.

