## Discussion

Based on a multi-centered community epidemiological study on TIA in Chinese adults, the prevalence of TIA in the Chinese population is as high as 2.4%. The number of patients with TIA in China is as high as 10–12 million (Liu et al., 2007). MRI-based hypoperfusion in patients with TIA is closely related to the time of completing MR imaging. A recent study has shown that hypoperfusion, detected by MRI, is present in 42.4% (25/59) of patients with TIA, and the median (IQR) time of symptom onset to baseline MR-PWI was 5 (4–9) days (Wang et al., 2019a). This is similar to the results of a previous study that has demonstrated the presence of hypoperfusion in 42% (57/137) of patients with TIA, with a median time of 9.2 h from symptom onset to completing MR-PWI (Asdaghi et al., 2013). When the time from symptom onset to the first PWI was shortened, such as a median time of 287 (136–591) min, the presence of hypoperfusion decreased to 25% (16/64) (Lee et al., 2017).

A recent study has shown an incidence of 7.4% of 90-day recurrence of stroke after TIA (Najib et al., 2019). There are multiple potential clinical risk factors for MR perfusion abnormality in the context of TIA. Insufficient local tissue perfusion may be the cause of recurrent TIA (Wang et al., 2019a,b).

This study has its own limitations. First, all the patients were recruited from the same city (Shanghai), and there may be bias in-patient selection. Second, the number of participants is relatively small. Third, treatments for patients with TIA might be slightly different, which will influence the likelihood of TIA recurrence.

The REATTACK trial will provide the power of predicting recurrent vascular events on days 7 and 90 based on hypoperfusion observed on PWI, which is completed within 24 h after symptom onset. This will guide the implementation of effective therapeutics for secondary prevention of TIA and/or stroke.

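### Baseline PWI is timed in two incompatible ways beside a 7-day entry window, so the share of the onset-based 7-day outcome window that follows the scan is not fixed

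*Protocol article*

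**What the plan says.** - **Entry.** Study Design: "The participants are patients who had TIA within 7 days of onset diagnosed by two neurologists". The Abstract agrees: "Ninety patients aged ≥18 years with recent (<7 days after onset) clinical TIA will be continuously included". Inclusion Criteria also allow presentation up to 7 days after onset.
- **Primary outcome.** Abstract: "The primary clinical outcome will be the recurrence of TIA within 7 days after the onset of TIA". Study Design and Primary Objective name a 7-day horizon without stating where it starts.
- **Baseline scan, admission-based.** Study Design: "Brain DWI and PWI assessments will be completed within 24 h of admission".
- **Baseline scan, onset-based.** Abstract: "perfusion-weighted imaging (PWI) assessments within 24 h after the onset of TIA". Procedures: "The first PWI will be completed within 24 h after onset, and the subsequent PWI will be completed on the 7th day ± 2". The closing paragraph of the Discussion describes the predictor as a scan done in the first 24 h after symptom onset.
- **Table 1.** The 24-h-from-onset label heads the screening column. PWI sits under Visit 1 with no hour limit, so the table does not itself fix the time of the scan.
- **Endpoint collection.** Table 1, footnote c: "AEs of interest and endpoints will be collected from the time of admission to the hospital". Recurrence is recorded at Visits 2 and 3.

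The text does not say how a recurrence between onset and the baseline scan is handled.

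**The concern.** The primary objective is to find out whether hypoperfusion on PWI helps to predict recurrence within 7 days. That requires the scan to come before the events and patients to have comparable time at risk after it. With entry up to day 7, an outcome clock that starts at onset and a scan timed from admission, neither condition is secured.

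A recurrence before the scan cannot have been predicted by it, and it might itself affect the perfusion finding that assigns the group. A patient scanned late has little of the window left and will tend to count as recurrence-free whatever the scan shows. The logistic model in Statistical Analysis cannot undo the counting of events that precede the exposure. The Discussion's intended conclusion, prediction from a scan in the first 24 h after onset, would not describe the patients whom the entry and admission-based rules let in.

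**Working it through.** **1. Can the rules hold together?** A patient who presents on day 3 satisfies the entry criterion. The admission rule puts the scan between day 3 and day 4; the onset rule required it by day 1. The same conflict arises for every presentation later than 24 h after onset. Either the entry window or the onset-based imaging rule has to give way.

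**2. Share of the onset-based window past at the scan.** Let e be days from onset to admission and l the lag from admission to scan in days. I take admission to be the day of presentation.

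Share past = min(1, (e + l)/7)

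- Onset rule: e + l ≤ 1, so the share is 0 to 1/7 = 14%.
- Admission rule: e from 0 to 7 and l from 0 to 1, so the share is 0 to 100%.

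| Entry day | Share past, l = 0 | Share past, l = 1 | Days left |
|---|---|---|---|
| 0 | 0% | 14% | 7 to 6 |
| 3 | 43% | 57% | 4 to 3 |
| 5 | 71% | 86% | 2 to 1 |
| 6 | 86% | 100% | 1 to 0 |
| 7 | 100% | 100% | 0 |

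An average needs an entry-time distribution, which the article does not give. Purely as an assumption, entry spread evenly over days 0–7 gives a mean share of 50% with no lag, 57% with a lag spread evenly over 0–24 h, and 63% with a 24 h lag.

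**3. What happens to a recurrence before the scan?** Footnote c starts endpoint collection at admission.

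- Onset to admission: not collected as an endpoint, so missed.
- Admission to scan, up to 24 h: collected, and nothing excludes it from the outcome, so it can count as predicted.

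**4. Relation to the sample size.** The stated 90 uses 10% against 34.8%, two-sided 0.05, 80% power, 1:1 and 5% dropout. The arcsine formula gives 42 per group, and 84/0.95 = 88.4, so 89. The unpooled-variance formula gives 87 and the pooled formula 93. Power is 81.7% at 45 per group and 79.6% at 42.75 (45 × 0.95). The figure is reproduced closely enough and is not challenged here.

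**5. Illustration of a shortened window.** Assume that both planning rates apply to the 7-day outcome, that events are spread evenly over the 7 days, and that only events after the scan count. The pooled formula is used throughout, so the full-window comparator is 93.

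- 6/7 of the window left: 10% × 6/7 = 8.6% and 34.8% × 6/7 = 29.8%. Power at 43 per group is about 71%, and the total needed is about 112.
- Half of the window left: 5% and 17.4%. Power is about 45%, and the total needed is about 213.

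With a constant hazard in place of an even spread, the results are about 74% and 106, and about 52% and 177. These figures show sensitivity only; they do not forecast this trial.

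**The case against.** **Most of the text uses the onset rule.** The Abstract, Procedures and Discussion all do, and under it at most 14% of the window precedes the scan. This stands, and it is why one cannot say that much of the risk window lies before PWI. It does not remove the conflict, because the 7-day entry criterion is stated in three places and cannot operate beyond day 1 under that rule.

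**The onset clock is explicit only in the Abstract.** True. Elsewhere the origin is unstated, which supports fixing it rather than leaving it alone.

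A reader might also infer four stronger things that the documents do not support:

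- *Half of the patients would have at most 2/7 = 29% of the window left.* This takes the Discussion's "time of symptom onset to baseline MR-PWI was 5 (4–9) days" as this trial's timing. It belongs to an earlier study whose upper quartile is 9 days, whereas the latest scan possible here is day 7 + 1 = 8. The two distributions cannot be the same.
- *Late imaging is shown to raise PWI positivity.* The Discussion says that the two are related and contrasts 25% at a median of 287 min with 42.4% at a median of 5 days. It also reports 42% at a median of 9.2 h. Its figures show essentially no difference between 9.2 h and 5 days, the range that matters most for late entrants.
- *All recurrences before the scan count as predicted.* Footnote c limits these to the interval from admission to scan, at most 24 h under the admission rule. Earlier ones are missed, which is a different fault.
- *A Visit 2 on day 5 loses the last two days of the window.* Recurrence is also recorded at Visit 3, so these events are recoverable if they are dated.

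**Conclusion.** The point holds as an internal contradiction that bears on the primary outcome. Entry up to 7 days and an admission-based scan cannot be squared with a scan within 24 h of onset, and the Abstract's outcome clock runs from onset whichever rule applies. The size is a range: 0–14% of the window past at the scan under the onset rule, and 0–100% under the admission rule. Where a trial patient falls depends on an entry-time distribution that the article does not give.

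Followed as written, the admission rule gives patients unequal time at risk after the scan, misses recurrences before admission and can credit the scan with events up to 24 h before it. The entry and admission-based rules then do not support the Discussion's claim about prediction from a scan in the first 24 h after onset. The direction of any bias in the PWI comparison is not established, and nothing here shows that 90 is the wrong sample size.

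**What to change.** - Reconcile the Abstract, Study Design, Inclusion Criteria, Procedures, Table 1 and Discussion so that one entry rule and one PWI-timing rule apply throughout. Which timing to adopt is for the investigators.
- Define the primary outcome as recurrence after the baseline PWI and within 7 days of it, using recorded event dates and times. Treat earlier events as baseline history.
- State the origin of day 7 for Visit 2. Where that visit falls before 7 full days from the scan, confirm 7-day status at Visit 3 or by telephone.
- If late presenters stay eligible, adjust the primary comparison for onset-to-PWI time.

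The cost is amendment wording and a case report form field for event date and time. There are two real downsides. Events before the scan stop counting as outcomes, by a number that depends on the unknown entry times. The outcome also becomes risk over 7 days from the scan rather than from onset: for a patient scanned on day 6 the window would run to day 6 + 7 = 13 after onset. Results would then be less directly comparable with onset-based recurrence figures such as those in the Background. Event dates should be captured from the start, because undated events may not be recoverable later.

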### Objectives

#### Primary Objective

▪   To assess the added diagnostic value of hypoperfusion demonstrated on PWI in predicting recurrent vascular events of patients with TIA within 7 days.

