### Sample Size and Power Calculation

Two-sided chi-square test is performed at *P* = 0.05 (alpha) to compare the incidence of recurrent vascular events between patients with TIA with PWI-positive and PWI-negative findings. Previous studies have shown that 10% of patients with TIA will relapse; however, the pilot study showed that 34.8% of PWI-positive patients with TIA had recurrent TIA. With the testing power of 80%, the significance level of 0.05 (two-sided), and a 1:1 ratio, with a dropout rate of 5%, a total of 90 patients are needed to detect the difference in relative risks between patients with TIA with PWI negative and PWI positive findings.

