### Statistical Analysis

The proportion of patients with recurrent vascular events on days 7 and 90 will be presented as frequency (percentage). Continuous variables will be presented as mean ± SD or median with interquartile range (IQR). Categorical parameters are presented as independent proportions. Baseline information of patients with or without hypoperfusion abnormalities is compared using the Mann-Whitney *U*-test or *t*-test for continuous variables and Fisher's exact test or χ^2^ for categorical variables. Logistic regression analysis will be performed to compare the proportion of recurrence between the two groups. *P* < 0.05 (two-sided) is considered statistically significant. Data analysis will be performed using IBM SPSS (version 20.0) for Windows (SPSS Inc., Chicago, IL, USA). The Data and Safety Monitoring Board will conduct an interim analysis on 45 patients (half of the required sample size). *P* < 0.05 is considered statistically significant in the interim and final analyses.

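### The primary objective is the added value of PWI, but the comparison that sizes the study is unadjusted, and no stated analysis compares prediction with and without PWI

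*Protocol article*

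**What the plan says.** The Primary Objective section of the Protocol article reads: "To assess the added diagnostic value of hypoperfusion demonstrated on PWI in predicting recurrent vascular events of patients with TIA within 7 days". It names no comparator.

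Three places describe how recurrence will be analysed:

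- Sample Size and Power Calculation: "Two-sided chi-square test is performed at *P* = 0.05 (alpha) to compare the incidence of recurrent vascular events", between the PWI-positive and PWI-negative groups.
- Abstract: "A chi-square test will be performed to compare the difference in the incidence of recurrent TIA between the two groups", and beside it "Multivariate logistic regression will be simultaneously performed to analyze the risk factors for the recurrence of TIA".
- Statistical Analysis: "Logistic regression analysis will be performed to compare the proportion of recurrence between the two groups".

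None of these names a covariate, and none is labelled the primary analysis.

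The markers against which a gain could be measured are collected. Table 1 schedules the ABCD2 score at screening. On DWI, the Study Design section says "Brain DWI and PWI assessments will be completed within 24 h of admission". The Background presents ABCD2 as an existing way to stratify risk, of low specificity for neurology professionals, and says that DWI-negative status does not settle perfusion status.

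**The concern.** An objective of added value asks whether PWI improves prediction once the information available at presentation has been used. A two-group comparison of recurrence asks only whether PWI status and recurrence are associated. The second can be true when the first is false.

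The groups here are formed by the scan result, so they may also differ in clinical risk. The Background gives a reason to expect this. The earlier cohort's reported independent risk factor was limb fatigue combined with the Tmax deficit (adjusted OR 3.74, 95% CI 1.02–13.64), so the perfusion signal came jointly with a clinical symptom, and clinical symptoms are an ABCD2 component. If PWI-positive patients carry higher ABCD2 scores, a significant chi-square could arise with no contribution from PWI beyond ABCD2. The report could then claim added value on evidence of association alone.

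**Working it through.** **1. The plan's own figure.** Inputs from Sample Size and Power Calculation: 10% ("Previous studies have shown that 10% of patients with TIA will relapse"), used here for the PWI-negative group; 34.8% in PWI-positive patients; two-sided 0.05; 80% power; 1:1; 5% dropout.

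n per group = [1.960·√(2·p̄·(1−p̄)) + 0.842·√(p₁(1−p₁)+p₂(1−p₂))]² / (p₂−p₁)², with p̄ = (0.10 + 0.348)/2 = 0.224.

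= [1.960·√0.3476 + 0.842·√0.3169]² / 0.248² = 43.17.

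Total 86.3; divided by 0.95, 90.9. The stated 90 is reproduced to within one patient (rounding up to 44 per group first gives 93). It is the size for the crude contrast and nothing else. With 90 × 0.95 = 85.5 evaluable patients the power is 79.6%.

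**2. Events available.** At the planning rates, 43 × (0.348 + 0.10) = 19.3 events among 86 evaluable patients. The section gives no time horizon for these rates. The follow-up of 46 patients in the Background lasted 3 months, and (14 + 2)/46 = 34.8%, which suggests a 3-month figure. The documents give no ratio of 7-day to 3-month TIA recurrence. As an assumption, the Background's stroke risks (4–10% at 7 days, 10–20% at 90 days) give 4/10 = 0.4 and 10/20 = 0.5. Then 19.3 × 0.4 = 7.7 and 19.3 × 0.5 = 9.6, so about 8 to 10 events.

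**3. Can the crude test mislead about added value?** An illustration with 43 patients per group and 3,000 simulations per row. Recurrence depends only on a binary high-risk marker; PWI adds nothing beyond it. All inputs are assumptions.

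| Marker present, PWI+ / PWI− | Recurrence with / without marker | Crude test significant | Likelihood-ratio test of PWI added to marker significant |
|---|---|---|---|
| 70% / 30% | 34.8% / 10% | 19% | 6% |
| 80% / 20% | 34.8% / 10% | 40% | 6% |
| 80% / 20% | 40% / 5% | 67% | 6% |

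The added-value test stays near its nominal 5%; the crude test does not.

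**4. Power for an adjusted PWI effect at N = 90.** The documents do not say how strongly PWI status overlaps with ABCD2 and DWI, so ranges are shown.

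(a) Crude odds ratio kept: (0.348/0.652)/(0.10/0.90) = 4.8. Let R² be the share of variation in PWI status explained by the base markers. The effective n per group is 42.75·(1 − R²), and the required N is 88/(1 − R²), rounded up, then divided by 0.95.

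| R² | Power at N = 90 | N for 80% |
|---|---|---|
| 0.05 | 77% | 98 |
| 0.10 | 75% | 104 |
| 0.20 | 70% | 116 |
| 0.30 | 64% | 133 |

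(b) Adjusted odds ratio smaller than crude, 10% reference rate, no variance inflation: OR 3.74 gives 62% power (N 139), OR 3.0 gives 45% (N 211), OR 2.0 gives 19% (N 596). The 3.74 is borrowed from the Background, where it describes a combined predictor, so it serves only as a scale.

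**The case against.** Four points on the other side have weight.

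- A reader might infer that the plan never adjusts for ABCD2 or DWI. The documents do not show that. The Abstract plans a multivariate regression and the Statistical Analysis section a logistic regression, both without a covariate list, and such a list may sit in an analysis plan that is not shown. What stands is that the multivariate model's stated aim is risk factors. Even with ABCD2 in it, an independent association is not a measure of gain in prediction.
- A reader might also infer that chi-square and logistic regression contradict each other, or that a wrong test has been designated primary. No test is called primary. With one binary predictor the Pearson chi-square is the score test of the logistic model, so an unadjusted regression agrees with it in substance. The need is to name one analysis.
- It is tempting to say that the risk-factor regression will overfit. The number of covariates is not stated, so this cannot be shown. The event count only limits what a model could carry.
- The concern leans on one word. Elsewhere the article speaks of correlation or of predictive power, so rewording the objective is a legitimate repair.

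DWI may also be unusable as a covariate. The Background defines TIA as without acute infarction, while the Abstract speaks of clinical TIA; if DWI-positive patients do not enter, DWI status does not vary. In the authors' earlier cohort it did vary: 21 of the 33 hypoperfused patients were DWI-negative.

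**Conclusion.** The point holds in this form: the primary objective claims added value, the only powered comparison is crude, and no stated analysis sets prediction with PWI against prediction without it. A significant result from the powered comparison would support association, not the stated primary claim. The data remain usable and the repair is cheap, so this is a change that should be made rather than a fatal flaw.

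The mismatch itself follows from the text and needs no assumption. Its numerical consequences do. The 19 events rest on the planning rates. The 8 to 10 rest on those rates being 3-month rates and on an assumed ratio of 0.4 to 0.5 taken from stroke risks. The adjusted power of 64% to 77% rests on R² between 0.30 and 0.05 with the crude odds ratio unchanged. The 19% to 67% false signals come from an illustration and do not estimate this trial.

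**What to change.** Choose one of two routes.

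**Keep the added-value objective.** Name one primary analysis: a logistic model for 7-day recurrence with ABCD2 as a single score, fitted without and then with PWI status. Add DWI status only if it varies and events allow. Use penalised estimation (Firth) if events are few, and hold the model to two or three terms. Test PWI by the likelihood ratio and report its adjusted odds ratio with 95% CI. Give the change in discrimination as descriptive only, since it will be imprecise with so few events. Keep the chi-square as the unadjusted supporting result.

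**Or reword the objective** as the association between hypoperfusion and 7-day recurrence, and make no claim of added value.

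Neither route needs new data. The first costs power and precision: at N = 90 the adjusted test falls short of 80% under every assumption examined. The sample-size section should therefore say that the 80% applies to the unadjusted comparison only. The team should also check that its named software offers penalised estimation. The second costs only the stronger claim.
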